## **4.0 Study Endpoints**

4.1 The primary outcome is the rate of recurrent pilonidal disease at 1 year defined as development of a new pilonidal abscess, folliculitis, or draining sinus after treatment, which would require antibiotic treatment, additional surgical incision and drainage, or excision within 1 year of enrollment.

Secondary outcome include: differences in disability days of the patient at 1 year, disability days of the caregiver at 1 year, HRQOL, health care satisfaction, disease-related attitudes and perceived stigma, rates of

PROTOCOL TITLE: A randomized controlled trial of laser hair depilation in adolescents with pilonidal disease

pilonidal disease-related complications, rates of pilonidal disease related procedures (incision and drainage), surgical excision, and post-operative complications, and rates of compliance with recommended treatment.

A summary of the outcomes that will be assessed are listed in the table below (Table 2).

**Table 2: Outcomes to be assessed**

| Outcome                                          | Initial visit | 1 month | 2 month | 3 month | 4 month | 6 month | 9 month | 12 month | 18 month | 24 month |
|--------------------------------------------------|---------------|---------|---------|---------|---------|---------|---------|----------|----------|----------|
| Pilonidal disease recurrence (Primary Outcomes)  | X             | X       | X       | X       | X       | X       | X       | X        | X        | X        |
| Disability days of the patient                   | X             | X       | X       | X       | X       | X       | X       | X        | X        | X        |
| Disability days of the caregiver                 | X             | X       | X       | X       | X       | X       | X       | X        | X        | X        |
| Compliance with recommended treatment            | X             | X       | X       | X       | X       | X       | X       | X        | X        | X        |
| Pilonidal disease related complications          | X             | X       | X       | X       | X       | X       | X       | X        | X        | X        |
| Emergency Department visits                      | X             | X       | X       | X       | X       | X       | X       | X        | X        | X        |
| Readmissions                                     | X             | X       | X       | X       | X       | X       | X       | X        | X        | X        |
| Additional surgical or interventional procedures | X             | X       | X       | X       | X       | X       | X       | X        | X        | X        |
| Post-operative complications                     | X             | X       | X       | X       | X       | X       | X       | X        | X        | X        |
| Healthcare-associated costs                      | X             | X       | X       | X       | X       | X       | X       | X        | X        | X        |
| Incremental cost-effectiveness                   |               |         |         |         |         |         |         | X        |          |          |
| Satisfaction with Health Care                    |               | X       |         |         | X       |         | X       |          |          |          |
| Health Related Quality of Life                   | X             |         |         | X       |         | X       |         | X        |          |          |
| Disease-related stigma                           | X             |         |         | X       |         |         | X       |          |          |          |
| Disease-related attitudes                        | X             |         | X       |         |         | X       |         | X        |          |          |

4.2 Data will be monitored by research team members once a week to ensure that all data (clinical data and questionnaires) collected are correctly completed. The proportion of patients that have a study related SAE (second degree burn or pain score >8) will be calculated after every group of 10 patients have completed their course of treatment. If the lower limit of the 95% confidence interval for this proportion exceeds 10%, the trial will be stopped. A Data Safety and Monitoring Committee (DSMC) has been formed and will meet every 6 months throughout the period during which patients are being recruited and through their first year of follow-up. The DSMC will review data provided by the primary study statistician and other study staff involved in data management and analysis. [name] (pediatric surgeon, Seattle Children's Hospital) will act as the chairman of the DSMC, and will serve alongside [name] (pediatric surgeon, Vanderbilt) and [name] (Statistician/Researcher, Nationwide Children's Hospital). The study principal investigator will be made aware of all adverse events as they occur and a quarterly review of all adverse events (AEs) that occur in the trial will be performed by the study team. All unexpected non-serious AEs and SAEs relating to participation in the study will be reported verbally and in writing to the study PI and NCH IRB. The verbal report will occur within 48 hours of the occurrence. The written report of a SAE (e.g., death or life-threatening adverse event) will be reported within 7 days.

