**Table 3. Number of patients with an SAE needed to stop the study early:**

| Number of laser treatment patients | If this many or more with an SAE, the study will be stopped | 95% LCL if this number with an SAE | 95% UCL if this number with an SAE |
|------------------------------------|-------------------------------------------------------------|------------------------------------|------------------------------------|
| 10                                 | 3                                                           | 0.103                              | 0.608                              |
| 20                                 | 5                                                           | 0.108                              | 0.473                              |
| 30                                 | 7                                                           | 0.115                              | 0.412                              |
| 40                                 | 8                                                           | 0.102                              | 0.350                              |
| 50                                 | 10                                                          | 0.111                              | 0.332                              |
| 60                                 | 11                                                          | 0.104                              | 0.301                              |
| 70                                 | 13                                                          | 0.111                              | 0.294                              |

An interim analysis is planned when a quarter of the planned total patients (26 patients in each group) have completed their 1 year follow-up and a final analysis will be performed when all patients have completed 1 year of follow up. These two analyses have been unequally spaced in order to ensure that the interim analysis is performed before study enrollment is complete. The interim analyses will be interested in assessing futility of the primary endpoint; the trial will be monitored based on the primary outcome of the proportion of patients with recurrent pilonidal disease and will employ the error spending function approach described by Lan and Demets and the error spending function described by O'Brien and Fleming.

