Throughout the trial, the rate of pilonidal disease recurrence at 6 months and 1 year and the tolerance of laser treatments will be monitored for safety. Tolerance to the laser treatments will be monitored by examining for study related serious adverse events (SAE) which include severe pain (defined as a maximum pain score of 8 or above during or within 24 hours of treatment) or second degree burns. The rates of SAEs will be calculated after every group of 10 patients has completed the course of treatment. The percentage of patients with either a second degree burn or a maximum pain score of 8 or above during or after treatment will be estimated. If the lower 95% confidence limit of this proportion exceeds 10%, the trial will be stopped (see Table 3 in the Protection of Human Subjects section for the stopping threshold at each interim safety analysis). The 10% level was chosen based on input from patients involved in our feasibility and tolerability pilot in which they expressed that even if they had experienced a high pain score or minor burn, they would like to continue receiving therapy as these both are self-limited events with minimal long term morbidity. These rates will be regularly reported to the Data and Safety Monitoring Committee (DSMC).

To verify the incident of a suspected recurrence during the course of the study, staff may request that the patient consent to release their protected health information from external entities. This would require the patient or the patient's personal representative to sign an MR-9 Authorization form.

Any adverse events such as an inability to tolerate the laser therapy or a recurrence will be tracked. Since recurrence is an expected adverse event it will not be reported; however, it will be monitored and if we detect an increased rate of recurrence with laser therapy, this will be reported and the trial will be stopped. Mild to moderate pain (pain score 7 or lower) secondary to laser therapy is also consider an expected adverse event and will not be reported. SAEs due to laser treatment include severe pain (pain score 8 or higher) and deep second degree burns.

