#### Baseline Assessment

Prior to the first treatment, both the patient and legal guardian will be asked to provide demographic and socioeconomic information (SES) including: age, race, ethnicity, gender, annual household income range, patient occupation (from those who work), guardian occupations and specific insurance coverage status. We will also collect a complete medical history of pilonidal disease, family history of pilonidal disease, current pilonidal disease symptoms, current hygiene regime, and history of physician office visits, Emergency Department/urgent care visits and inpatient hospitalizations for pilonidal disease.

The child and legal guardian will be asked to complete the age appropriate PedsQLTM Quality of Life Inventory and questions about healthcare associated disability, pain and pilonidal disease management. The patient will also complete the Child Attitude Toward Illness Scale (CATIS) and the parent and child will complete the disease-related stigma scales. To assist with the costs and time spent participating in the study, parking

484 costs will be paid for by the study and a \$20 research debit card will be  
485 given to the patient or their legal guardian at the end of the visit.

486 **Immediately Following/ 24hrs Post-Treatment (Intervention Group)**

487 Immediately following each laser treatment and 24 hours after, the patient  
488 will be asked to rate their pain from 1-10 utilizing the Numeric Rating  
489 Scale (NRS-11) (see Appendix for Pain Scale). Contact for the 24 hour  
490 follow-up will be completed by phone, text or email.

491 **Follow-up at 1, 2, 3, and 4 months**

492 The patient and legal guardian will complete surveys assessing healthcare  
493 associated disability, pain, pilonidal disease management, and Emergency  
494 Department/ urgent care/ physician office/hospital visits that occurred  
495 between follow-up assessments. In addition, the CATIS will be completed  
496 at the 2 month follow-up, the parent and child disease-related stigma  
497 scales will be completed at the 3 month follow-up, and the age appropriate  
498 Child and Parent PedsQLTM will be administered at the 4 month follow-  
499 up. The Healthcare Satisfaction questionnaire will be administered at the 1  
500 and 4 month follow-ups. These surveys and questionnaires will be  
501 completed at the in-person visits for patients in the laser group and by  

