### 12.0 Local Number of Subjects

12.1 The sample size needed to assess the primary outcome of the proportion of patients with recurrent pilonidal disease at 1-year is based on: 1) previous published studies and institutional data on the recurrence rates of pilonidal disease and 2) the efficacy of laser hair depilation treatment to reduce pilonidal disease recurrence in previous studies and our institutional pilot study. In this RCT, the recurrence rate within 1 year is expected to be 12% in the control group and a maximum 2% in the laser group. Based on these estimated recurrence rates, under a group sequential design with one interim and one final analysis, an overall type I error rate (two- sided) of 5 % and power of 80%, the sample size required for this trial is 122 patients in each treatment group. Assuming a 10% drop out rate over the course of the 1 year follow-up, we will plan to enroll 136 patients in each group (total; n=272 patients).

The gap in the laser treatments caused by COVID-19 created a gap in when we could begin laser treatments in newly enrolled patients by 1-3 months. Since a laser patient's participation in the study begins at their first laser treatment, no data has been collected on these patients. Patients in the group have reported no longer being interested/able to receive

treatments due to concerns about COVID and visits to the hospital to receive laser treatments. This group of about 15 patients was not anticipated for our sample size calculation but are needed for the primary outcomes data. In order to maintain the required power in our analyses, our statistician recommends enrolling and randomizing an additional 30 patients, thereby increasing our sample size to 302 patients (151 in each group).

12.2 If applicable, distinguish between the number of subjects who are expected to be enrolled and screened, and the number of subjects needed to complete the research procedures (i.e., numbers of subjects excluding screen failures.) -N/A

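### One of the two statements of the laser stopping rule counts pain >8 instead of 8 or above, so followed literally it can miss the patient who triggers the stop.

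*Combined protocol and SAP*

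**What the plan says.** Section 4.2 (under 4.0 Study Endpoints) gives a binding stopping rule for laser tolerance in two places. Both apply it after every 10 patients who complete treatment, and both stop the trial if the lower 95% confidence limit of the event proportion exceeds 10%.

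- **Paragraph after Table 2:** "The proportion of patients that have a study related SAE (second degree burn or pain score >8) will be calculated". This paragraph does not refer to Table 3.
- **Text after Table 3:** the quantity estimated is "The percentage of patients with either a second degree burn or a maximum pain score of 8 or above during or after treatment". Its boundary sentence points to the table: "the trial will be stopped (see Table 3 in the Protection of Human Subjects section for the stopping threshold at each interim safety analysis".

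The text after Table 3 also defines the serious events as "severe pain (defined as a maximum pain score of 8 or above during or within 24 hours of treatment) or second degree burns", and says "Mild to moderate pain (pain score 7 or lower) secondary to laser therapy is also consider an expected adverse event". Its closing list of laser SAEs again puts severe pain at 8 or higher.

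Table 3 gives stopping counts for 10 to 70 laser patients under the column heading "If this many or more with an SAE, the study will be stopped". It does not say which pain score makes an SAE.

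Pain is collected in section 6.4, immediately after each session and 24 hours later, when the patient "will be asked to rate their pain from 1-10 utilizing the Numeric Rating" Scale.

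**The concern.** On a scale collected in whole numbers, above 8 means 9 or 10, while 8 or above means 8, 9 or 10. The two statements therefore disagree about any patient whose worst score is exactly 8 and who has no second degree burn. Taken on its own, the first statement does not count that patient as an SAE, although the later text does not accept the score as expected pain either.

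This is the numerator of a rule that stops the trial, and the participants are aged 11 to 21. A reader who works through section 4.2 in order meets the >8 definition just before a table that counts only an unspecified SAE. Staff who tally on that definition could continue laser treatment where the later text and Table 3 require a stop.

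**Working it through.** **1. Reproduce Table 3.** The printed limits match the two-sided 95% Agresti-Coull interval. For x events in n patients, with z = 1.96:

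- n' = n + z²
- p' = (x + z²/2) / n'
- lower limit = p' − z·√(p'(1 − p')/n')

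For 3 of 10: n' = 13.84, p' = 4.92/13.84 = 0.3555, lower limit = 0.3555 − 0.2522 = 0.103, as printed. The smallest counts with a lower limit above 0.10 are 3, 5, 7, 8, 10, 11 and 13, the same as in Table 3. All 14 printed limits agree to within 0.001, so the table is correct.

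**2. Remove one event at each look.** This is the effect of not counting one patient whose worst score is exactly 8.

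| Laser patients | Stopping count | Lower limit (printed) | One event fewer | Lower limit |
|---|---|---|---|---|
| 10 | 3 | 0.103 | 2 | 0.046 |
| 20 | 5 | 0.108 | 4 | 0.075 |
| 30 | 7 | 0.115 | 6 | 0.091 |
| 40 | 8 | 0.102 | 7 | 0.084 |
| 50 | 10 | 0.111 | 9 | 0.095 |
| 60 | 11 | 0.104 | 10 | 0.091 |
| 70 | 13 | 0.111 | 12 | 0.099 |

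At every look the lower limit falls below 0.10, so one such patient is enough to reverse the decision. This step needs no assumption about rates.

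**3. Chance that the two wordings disagree.** The documents give neither the SAE rate nor the share of patients scoring exactly 8. The 13-patient pilot (section 2.2) reports no second degree burns and no pain scores. Both rates below are therefore assumed.

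Exact cumulative probabilities of stopping were computed with a look every 10 completers. The counts to 70 are those printed; beyond 70 the same interval rule is applied. The 120 horizon is an extrapolation built from section 12.0: 151 allocated to laser, less about 15 who may not start ("This group of about 15 patients was not anticipated for our sample size calculation"), is 136; less 10% dropout, 136 × 0.9 ≈ 122.

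| Per-patient event rate | Stop by 70 | Stop by 120 |
|---|---|---|
| 4% | 0.7% | 0.7% |
| 5% | 1.3% | 1.3% |
| 10% | 12.5% | 14.5% |
| 13.5% | 33.4% | 44.4% |
| 15% | 44.9% | 60.3% |

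The >8 count can never exceed the count at 8 or above. The gap between the two stopping probabilities is therefore the probability that the wordings lead to opposite decisions.

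| Assumed split (burn or >8, plus exactly 8) | By 70: >8 vs 8 or above | By 120: >8 vs 8 or above |
|---|---|---|
| 10% + 5% | 12.5% vs 44.9% | 14.5% vs 60.3% |
| 13.5% + 1.5% | 33.4% vs 44.9% | 44.4% vs 60.3% |
| 4% + 1% | 0.7% vs 1.3% | 0.7% vs 1.3% |

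A joint simulation of the first row (400,000 runs) gave opposite decisions in 32.4% of runs by 70 and 45.8% by 120, in line with the differences 44.9 − 12.5 = 32.4 and 60.3 − 14.5 = 45.8.

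**The case against.** The best defence is that the two rules are nested. Everyone counted above 8 is also counted at 8 or above, and the first statement never says the trial continues if its own criterion is not met. Someone who obeys both statements applies the inclusive rule. The later text is also fuller, repeats its cut-off and cites the table, so the intent is plain and the >8 looks like a slip. That is probably true, and it is why the correction is easy. It does not remove the problem: nothing says the later text governs, and a tally made from the first statement alone gives a different decision.

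The rates are assumed, and nothing in the documents supports 15%. That stands. At low rates the wording hardly matters, and the figures at 70 completers are firmer than those at 120, because Table 3 ends at 70 and the 10% dropout refers to the year of follow-up, not to the treatment course.

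Two smaller points also stand. The closing SAE list qualifies the burn as deep, whereas both statements of the stopping rule say only second degree. And the rule refers to pain during treatment, while section 6.4 schedules scores only immediately afterwards and at 24 hours. Neither affects the conflict over the pain cut-off.

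**Conclusion.** The concern holds. The >8 cut-off in the paragraph after Table 2 conflicts with the rest of section 4.2 and should read 8 or above. The counts in Table 3 are right.

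That one patient scoring exactly 8 can reverse the decision at each printed look follows from the documents alone. The probability of a reversal rests on assumed rates: by 70 completers it is about 32 percentage points with 10% plus 5%, about 11 to 12 with 13.5% plus 1.5%, and 0.6 with 4% plus 1%. Because the rule is binding and the intended reading is clear, the text should be corrected, but this does not undermine the design.

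**What to change.** In the paragraph after Table 2, replace the >8 criterion with a maximum pain score of 8 or above during or within 24 hours of treatment. Put the same event, or a second degree burn, in the Table 3 heading. Then recount completed laser patients on that definition. While editing, it is sensible to align the burn wording in the closing SAE list and to say which recorded score stands for pain during the session.

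The cost is one phrase, one table heading and a recount from the scores already taken after each session and at 24 hours. The Table 3 counts do not change.

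The one downside is a higher chance of stopping than under >8. If the inclusive rate were 10% (5% plus 5%), a level the rule is meant to tolerate, the chance of stopping by 70 completers would rise from 1.3% to 12.5%. The text after Table 3 already prescribes that stop.
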